## 12.3 Stratification Factors

**Not applicable**

## 12.4 Analysis of Endpoints

### **12.4.1 Analysis of Primary Endpoints**

Feasibility will be assessed based on rates of recruitment, study conduct (intervention and enactment fidelity), retention and acceptability of the study. Descriptive statistics will be used to summarize recruitment rates for clinical and faith-based organizations separately. The screening-to-enrollment (STE) ratio will be defined and calculated as the proportion of people who consented to those for whom screening was attempted. The reasons for declining participation will be grouped into categories and the proportion described.

Adherence to several aspects (session attendance, dietary, physical activity and self-weights) of the intervention will be tracked. The proportion of coaching sessions attended by the index participant and social network member across the 24 weeks will be calculated separately. Additionally, a tally of each self-regulation behavior (total # of days weighing, total # of days self-monitoring dietary intake, & total # of days wearing fitness tracker) will be summarized.

Treatment fidelity will be summarized as an average of the proportion of treatment elements delivered correctly. A correlation (Pearson) between the self-reported checklist and objectively measured checklist will be conducted. The retention rate will be defined as the proportion of participants who complete the 24-week assessment among those who completed the baseline assessment. Sample sizes and the proportion of missing data will be calculated for each measure collected as baseline, follow-up visits and study completion. Chi-Squared tests (or Fisher's exact tests) and two-independent-sample t-tests (or Wilcoxon rank-sum tests) will be used, as appropriate, to examine whether baseline characteristics predict retention and to identify differences in dropout rates between the intervention and control group. The qualitative satisfaction data will be content analyzed. Two study personnel will generate a priori codes corresponding to the interview guide (e.g., reactions to enrolling network members). One study personnel will apply the coding scheme to each interview summary, and then the two will formalize agreement or disagreement regarding the derived codes.

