## 4.2 Inclusion Criteria Index Participant

1. Black race or Hispanic ethnicity

2. Male or Female 18 years of age or older

3. Calculated BMI > 30kg/m^2^ from objectively measured height and weight by study staff

4. Access & willingness to use program food intake app via home computer or a smartphone

5. Ability to identify at least one adult social network member who will participate in the study

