## 4.6 Lifestyle Considerations

**Not applicable**

## 4.7 Screen Failures

Screen failures are defined as participants who consent to participate in the clinical trial but are not subsequently randomly assigned to the study intervention or entered in the study. A minimal set of screen failure information is required to ensure transparent reporting of screen failure participants, to meet the Consolidated Standards of Reporting Trials (CONSORT) publishing requirements and to respond to queries from regulatory authorities. Minimal information includes demography, screen failure details, eligibility criteria, and any serious adverse event (SAE). Individuals who do not meet the criteria for participation in this trial (screen failure) because of an active enrollment in a weight loss program, food insecurity, or lack of clearance from a medical provider may be rescreened. Rescreened participants should be assigned the same participant number as for the initial screening.

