## 4.6 Strategies for Recruitment and Retention

Recruitment Strategies:

- An estimated 800 Black or Hispanic individuals 18 years of age or older will need to be screened in order to reach the target enrollment of 132 participants.
- The anticipated accrual rate is 8 participants per month (6% of target enrollment)
- Recruitment will take place at four outpatient clinic sites Weill Cornell Internal Medicine Associates, Weill Cornell Urology @ Brooklyn, Weill Cornell Urology @ Upper East Side, and Weill Cornell Primary Care at Lower Manhattan.
- Potential participants will be identified through a TRAC request in EPIC specific to those clinical sites. Study staff will contact the medical provider to verify that the participant is fit to potentially participate in the study and ask their permission to contact the potential participant. Participants will be contacted via phone call, email or regular mail based on their indicated preferences for communication in the electronic health record.
- Recruitment strategies will include mailing potential participants flyers describing the study with the study team contact information.

Retention Strategies:

- - Collection of monthly screening, enrollment, and retention logs
  - Index participants will be compensated $25 for each in person visit
  - Social network participants will be compensated $25 for each completed survey
  - Participants will receive text and call reminders for each scheduled visit

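### The screening-to-enrollment ratio counts everyone who consents as enrolled, including people who consent and then fail screening

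*Protocol*

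**What the plan says.** Sections 10.1 (Response Criteria) and 12.4.1 (Analysis of Primary Endpoints) list recruitment first among the components of feasibility. Both define the screening-to-enrollment (STE) ratio in the same words, "calculated as the proportion of people who consented to those for whom screening was attempted".

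Section 4.7 (Screen Failures) defines screen failures as "participants who consent to participate in the clinical trial but are not subsequently randomly assigned to the study intervention or entered in the study". It adds that people who fail "because of an active enrollment in a weight loss program, food insecurity, or lack of clearance from a medical provider may be rescreened", keeping their participant number.

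The screening visit in section 6.1.1 lists one item, informed consent. Section 4.2 requires BMI "from objectively measured height and weight by study staff", and anthropometrics first appear in the visit schedule at Visit 1, Week 0.

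The section on recruitment and retention strategies estimates that 800 individuals "will need to be screened in order to reach the target enrollment of 132 participants". Section 3.1 makes clear that these 132 are index participants to be randomised.

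Section 12.4.1 also asks for "recruitment rates for clinical and faith-based organizations separately". The recruitment section says "Recruitment will take place at four outpatient clinic sites", and the Protocol Summary names the same kind of sites and no others.

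**The concern.** The name of the ratio promises enrollment, but its numerator is consent. Section 4.7 keeps the two apart: a person can consent, fail an eligibility criterion and never be randomised. Under the STE definition that person still counts as a success. The ratio can therefore only equal or exceed the enrollment yield, and it exceeds it as soon as one consenter fails screening.

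The numerator is also not limited to index participants. Network members give consent too, so the phrase could be read to include people who were never candidates for randomisation.

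What is at stake is the accuracy of a reported feasibility figure. Under Stopping rules in section 15, the protocol says a goal is to obtain estimates for a larger trial. A yield that is really a consent rate would be a poor guide to how many people such a trial must screen.

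The site breakdown is a separate and simpler fault: it asks for a stratum in which the protocol plans no recruitment.

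**Working it through.** **Order of events.** Four places set side by side:

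- Section 6.1.1: consent is the only procedure listed at the screening visit.
- Section 4.2: eligibility needs a BMI measured by staff.
- Visit 1 (Week 0): the first scheduled anthropometrics and the social network survey.
- Section 7.11: randomisation follows the social network interview.

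So the schedule puts the BMI check after consent and leaves room for it to exclude someone before randomisation. By the section 4.7 definition, failures for weight-loss programme enrollment, food insecurity or lack of medical clearance are also failures of people who have consented.

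**The plan's own figure.** The protocol states no value or target for the ratio, so there is none to reproduce. The nearest figure is the recruitment estimate:

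randomised / screened = 132 / 800 = 0.165 = 16.5%.

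**The ratio as defined.** Let R = 132 randomised, S = 800 for whom screening is attempted (taking the 800 to be that group), and f = the share of consenting index participants who become screen failures. Then:

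- consented C = R / (1 - f)
- STE as defined = C / S = R / [S(1 - f)]
- STE as defined ÷ enrollment yield = 1 / (1 - f)

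The protocol gives no f, so the values below are assumptions. C is rounded up to whole people.

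| Assumed f | Consented C | Of whom screen failures | C / 800 | Factor |
| --- | --- | --- | --- | --- |
| 0% | 132 | 0 | 16.5% | 1.00 |
| 5% | 139 | 7 | 17.4% | 1.05 |
| 10% | 147 | 15 | 18.4% | 1.11 |
| 20% | 165 | 33 | 20.6% | 1.25 |
| 30% | 189 | 57 | 23.6% | 1.43 |

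Each post-consent screen failure adds 1/800 = 0.125 percentage points.

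**The breakdown.** Section 10.1 has the parallel sentence on recruitment rates without the faith-based split. The Protocol Summary and the recruitment section list only four clinic sites. The faith-based stratum would be empty.

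**The case against.** The strongest reply is that numerator and denominator are both written out, so a careful reader will know the figure is consented over screened and the fault is mainly one of label. Nothing is decided on it either: the three primary endpoint criteria in section 12.1 (75% attendance, 80% with a network member engaged, 85% completing the final assessment) do not use the ratio, and it has no threshold. That stands and limits the consequence. It does not rescue a measure whose name and definition disagree, in a protocol that itself separates consent from enrollment.

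A reader might infer more than the documents support:

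- *That all eligibility checks follow consent.* They do not. The recruitment section has staff identify candidates from records and ask the medical provider about fitness before any contact. Only some checks come later.
- *That the definition contradicts the 132-from-800 estimate.* It does not. That estimate is not labelled as the STE ratio, and the two describe different steps.
- *That reasons for exclusion are hidden.* Section 4.7 requires screen-failure details and eligibility criteria to be recorded for CONSORT reporting, and the recruitment section requires monthly screening and enrollment logs. The reasons are missing from the ratio, not from the data.
- *That a later trial would fall short by a definite number.* This would need an f that the protocol does not give, and planners who ignored the randomised count.

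**Conclusion.** The definition is wrong as written: a ratio named for enrollment counts people whom section 4.7 says were not enrolled. The direction is certain whenever any consenter fails screening. The size is not known. On the planned 132 of 800, assumed failure shares of 5% to 30% move the reported figure from 16.5% to between about 17.4% and 23.6%; with no such failures there is no difference. The damage is limited to the descriptive recruitment yield and any later planning that relies on it. No primary endpoint threshold is affected. The call for a faith-based breakdown is a separate wording error that does not depend on f.

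**What to change.** In sections 10.1 and 12.4.1, define the STE ratio as index participants randomised divided by unique individuals for whom screening was attempted, counting a rescreened person once under the number that section 4.7 already retains. Beside it, report two separate steps: the consent rate (index participants consented over screening attempted), and post-consent screen failures by criterion. Naming index participants in each numerator also keeps network members out of the count.

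In section 12.4.1, replace the reference to clinical and faith-based organizations with the four named clinic sites.

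The cost is wording only, since the logs and screen-failure data are already required. The reported ratio may be slightly less favourable.

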### **6.1.2 Treatment Phase**

Eligible participants will be randomly assigned to the social network intervention or control groups in a 1:1 ratio using a numerical randomization scheme developed by the statistical team. Following randomization, participants that are randomized to the social network intervention group will complete 3 in person communication skills sessions with their social network members during weeks 3, 5, and 15. Instead of completing communication skills sessions, participants randomized to the control group will complete regular virtual lifestyle coaching sessions with the study team that consists of the following topics: Keep your health healthy (week 3), Eat well away from home (week 5), and Social Cues (Week 15). All other sessions will focus on the topics below and will be the same across both treatment groups.

Note: The weeks that are not listed in the treatment phase below are weeks that will be treatment breaks.

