### **12.4.2 Analysis of Secondary Endpoints**

We will examine summary statistics, histograms, and scatter plots of the measured covariates and outcomes for outliers and data trends. Analyses of differences between those completing and not completing the study and the within-group changes during the intervention will be performed according to modified intention-to-treat principles. Multivariate linear regression (MLR) models will be used to examine the relationship between changes in the social network processes and exposure (the social network lifestyle intervention vs the lifestyle intervention), adjusted for covariates selected from univariate analyses; potential covariates for MLR are categorized by theoretical construct. We will also explore the effect of gender by including a three-way interaction (gender*social support*weight loss), although we recognize that we might not have enough power to detect such interactions.

To further explore the effect of the intervention, we will do sensitivity analysis: (1) Multivariable linear regression using weight loss as continuous outcome variables (a change in weight and percent weight change), adjusting for baseline covariates distributed differently between intervention groups; (3) test interaction terms between treatment group and other covariates; and (4) examine completers only.

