## Stopping rules

In this minimal risk lifestyle intervention trial, it is more likely that difficulty in recruiting adequate numbers of participants will require stopping the trial than that excess adverse events will occur and require stopping the trial. However, as outlined elsewhere, we will monitor injury rates in all participants and the safety officer, together with the study investigators, will alert the IRB and the NIH if a larger than reasonably expected event rate should occur in the treatment group. Other issues relating to stopping rules for this trial include:

New Information

It is exceedingly unlikely that any new information will become available during this trial that would necessitate stopping the trial.

Limits of Assumptions

It is possible that baseline differences between the groups, excessive study dropouts and/or missing data by the interim measurement time point will limit the value of data analysis of measurements at the 3-year time point. Baseline differences will be evaluated after the first measurement time point. Given the monitoring plans outlined elsewhere in this document, it is exceedingly unlikely that there will be baseline differences between groups of any magnitude to threaten the validity of the study.

While this R01 mechanism's primary aim is to determine the feasibility and acceptability of the intervention our goal is also to obtain appropriate estimates for a larger trial. Based on a sample size of 132 participants with an expected attrition of 15% we will have sufficient power (98%) to detect an 8-pound difference SD 10.4) between the intervention and control group (secondary outcome). Alert points are set at dropout rates of 30% (low alert), 40% (mid-alert), and 50% (high alert). As shown in the table below even at a high level alert we will still have moderate power (0.87) to determine our secondary outcomes.

| Dropout Rate  Alert level | 30%  low | 40%  mid | 50 %  high |
| --- | --- | --- | --- |
| Power available | 96% | 92% | 88% |

The actions taken at each level of alert are given below:

Low to mid-level alert = Conference call between study investigators to discuss approaches to minimize further losses to follow-up/dropouts.

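### The planned attrition checks cannot show whether different kinds of people leave each arm, which leaves the week-24 weight regression open to a modest, unseen bias

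*Protocol*

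**What the plan says.** Section 12.4.1 names chi-squared or Fisher tests and t or Wilcoxon tests, and gives their purpose: "to examine whether baseline characteristics predict retention and to identify differences in dropout rates between the intervention and control group". The arms appear only in the second half of that sentence.

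Section 12.4.2 returns to the subject with "Analyses of differences between those completing and not completing the study and the within-group changes during the intervention", to be done on modified intention-to-treat principles, again with no split of completers and non-completers by arm. The same section sets two adjustment rules. The models of social network processes adjust for covariates chosen by univariate analysis. The weight regression, listed as a sensitivity analysis, adjusts only for baseline covariates that turn out to differ between the arms. Treatment-by-covariate interactions and a completers-only analysis are also listed; both concern the outcome, not retention.

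The Stopping rules part of section 15 handles dropout as a single rate: "Alert points are set at dropout rates of 30% (low alert), 40% (mid-alert), and 50% (high alert"). It considers only the effect on power.

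Nowhere does the protocol compare those who leave one arm with those who leave the other.

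**The concern.** Randomisation makes the arms comparable at baseline. Dropout undoes this when leavers differ from completers in a different way in each arm. Equal dropout rates do not exclude that. Nor does a pooled comparison of leavers with completers, because opposite patterns in the two arms cancel.

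Different reasons for leaving are plausible here. Only the ROBUST arm attends sessions with network members at weeks 3, 5 and 15. The protocol itself mentions discomfort at disclosing personal matters in front of others (section 2.4.3) and embarrassment before friends and family (section 8.1).

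At stake is the week-24 weight difference. It is a secondary outcome, but the Stopping rules text says the trial should also supply estimates for a larger trial, so a shifted estimate would be carried forward.

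**Working it through.** **Inputs from the protocol.** Allocation is "control groups in a 1:1 ratio" (section 6.1.2). The power statement begins "Based on a sample size of 132 participants with an expected attrition of 15"% and continues "we will have sufficient power (98%) to detect an 8-pound difference SD 10.4" lb (Stopping rules). This gives 66 per arm, about 10 dropouts and 56 completers per arm.

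**Assumptions, not in the protocol.** Two-sided alpha is 0.05. One standardised baseline factor X differs by δ = 0.5 to 1 SD between leavers and completers, with opposite signs in the two arms. X correlates ρ = 0.3 to 0.5 with weight change. The weight difference is taken among those with a week-24 value, without X in the model.

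**1. The plan's own figures.** Power = Φ(8 / [10.4 × √(2/n)] − 1.96).

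| Dropout | n per arm | Computed | Stated |
|---|---|---|---|
| 15% | 56.1 | 98.3% | 98% |
| 30% | 46.2 | 95.9% | 96% |
| 40% | 39.6 | 92.8% | 92% |
| 50% | 33.0 | 87.8% | 88% |

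The stated powers reproduce, so the inputs are read correctly.

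**2. Imbalance and bias.** If both arms start with the same mean of X, completers in each arm shift by (10/66) × δ, in opposite directions. The imbalance is 2 × (10/66) × δ, and the bias is imbalance × ρ × 10.4 lb.

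| δ | Imbalance | Bias, ρ = 0.3 | Bias, ρ = 0.5 |
|---|---|---|---|
| 0.5 SD | 0.15 SD | 0.47 lb | 0.79 lb |
| 1 SD | 0.30 SD | 0.95 lb | 1.58 lb |

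This is 6% to 20% of the 8-lb difference. The standard error of the arm difference is 10.4 × √(2/56) = 1.97 lb, so the bias is at most 0.8 of a standard error.

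**3. What the checks see.** Under exact opposition the pooled difference in X is zero and the dropout rates are equal. The arm-by-completion contrast is 2δ, with standard error √[2 × (1/10 + 1/56)] = 0.486.
- δ = 1: z = 2/0.486 = 4.12, power about 98%. In simulation the pooled test rejects in about 4% of trials and the contrast in about 98%.
- δ = 0.5: z = 1/0.486 = 2.06, power Φ(2.06 − 1.96) = 54%.

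**4. A second model.** In a simulation of 3,000 trials per scenario, dropout was logistic in X with slope ±0.7 or ±1.0, at 15% in both arms, with no true effect. Both planned checks were passed in 88% to 90% of trials, against 90% with no selection at all. Bias was 0.6 to 1.4 lb, and the type I error of the unadjusted weight comparison was about 7% to 10%. The contrast rejected in 76% to 95%. At 30% dropout, the low alert, a slope of 0.7 gave a bias of 1.2 to 2.0 lb.

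**5. When opposition is incomplete.**
- 1 SD in one arm and 0.5 SD the other way: pooled test 16%, contrast 87%, imbalance (10/66) × 1.5 = 0.23 SD.
- 1 SD in one arm only: the pooled difference is 0.5 SD with standard error √(1/20 + 1/112) = 0.243, so z = 2.06. The contrast is 1/0.486, also z = 2.06. Power is about 54% for both.

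**6. Does the planned adjustment remove the bias?** With X in the outcome model the bias falls to 0.03 lb or less.
- Network-process models: univariate selection would pick up a factor with ρ = 0.3 in about 90% of trials, since atanh(0.3) × √109 = 3.23 and Φ(3.23 − 1.96) = 0.90.
- Weight regression: X enters only if it is judged to differ between arms. Among completers, a test flagged this in only 18% to 31% of the simulated trials at 15% dropout. A comparison at randomisation would not show it.

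**The case against.** The strongest reply is that these tests are not there to certify the week-24 comparison. They sit under the primary endpoints, which are feasibility thresholds that include completion of the final assessment. Asking what predicts retention, and whether it differs by arm, answers that aim. A reader might infer that the protocol offers the tests as evidence against attrition bias. It makes no such claim, and this part of the objection stands.

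The pooled reading is also an inference. It is the natural one, but the text does not forbid by-arm summaries, and an analysis plan could add them. The handling of missing week-24 weights may likewise be settled there; the protocol mentions modified intention-to-treat and measures weight at weeks 0, 8, 16 and 24. What remains is that the protocol names its attrition checks, and as named they do not ask the question that matters for the arm comparison.

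The scenario is constructed, and nothing in the documents shows that such selection will occur. One might conclude that the pooled test is generally blind; step 5 shows that its weakness is confined to opposing patterns. One might also conclude that all the secondary models are exposed; step 6 shows that univariate selection would usually protect the network-process models. Both limits stand, and they narrow the point to the weight regression.

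**Conclusion.** The point holds in a limited form. The attrition checks in sections 12.4.1 and 12.4.2 cannot tell whether different kinds of people leave each arm. At the expected 15% attrition, opposite selection of 0.5 to 1 SD on a factor correlating 0.3 to 0.5 with weight change would bias the unadjusted weight difference by about 0.5 to 1.6 lb, usually without either check reacting. That is below one standard error and concerns a secondary outcome. The weight regression is the main exposure, because its adjustment rule need not admit the factor responsible.

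The figures rest on the assumed selection strength, direction and correlations, on equal dropout in both arms, and on an analysis of those with week-24 weights. The documents do not support a claim that the trial's comparison is biased, nor any effect on the feasibility endpoints. This is an inexpensive improvement to the plan, not a flaw that undermines it.

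**What to change.** In section 12.4.1, keep the planned tests and add one table of baseline characteristics by completion status within each arm, with the arm-by-completion contrast for each characteristic.

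In section 12.4.2, add a sensitivity version of the week-24 weight model adjusted for a prespecified set of prognostic baseline covariates already collected under Table 1, for example baseline weight and the baseline network, self-efficacy and affect scores. Do not choose the covariates from dropout tests: with about 10 leavers per arm such a choice would be unstable and would ignore prognosis.

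The cost is one table and one model on existing data. The within-arm contrasts will be imprecise (about 54% power at 0.5 SD in opposite directions), so they should be read as description. Neither step protects against selection on unmeasured factors; Table 1 lists no motivation scale, for instance.
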